**Figure 2. fig2-17539447221108817:**
[figure not shown]
Visual representation of the PAD-specific exercise circuit.

**Figure 3. fig3-17539447221108817:**
[figure not shown]
The Intermittent Claudication rating scale which will be used by the
patients to grade claudication pain during the exercise intervention.
Taken from AACPVR Guidelines for Cardiac Rehabilitation and Secondary
Prevention Programs (2013).

### Randomisation and blinding

The random allocation sequence will be generated by the trial statistician on a
1:1 basis using a computer program random number generator. To ensure allocation
concealment, researchers will request randomisation from the principal
investigator on completion of all baseline assessments using a sealed, opaque,
sequentially numbered envelope. All outcome assessors will be blinded as will
the trial statistician. Exercise professionals delivering the interventions
cannot be blinded; however, they will not be involved in data analysis or
reporting.

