## Methods and analysis

This study is a single-centre randomised controlled trial. Participants will be
randomly allocated to 24 weeks of PF, MOD-P or MAX-P exercise with outcomes measured
at baseline (visit 1), 12 weeks (visit 2) and 24 weeks (visit 3). All sessions will
be supervised by a qualified exercise professional within an existing community
pathway. As this programme duration is longer than suggested in current UK
guidelines, outcomes will be measured at 12 and 24 weeks to ensure generalisability
of the findings to UK SEPs.

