### Sample size

Power analysis performed in G*Power^
31
^ showed that 39 patients (total) would be needed to attain statistical
significance. Based on previously published data investigating a UK-based SEP
that adopted a similar exercise circuit^
32
^ and converting the interquartile range to standard deviation,^
33
^ a median change in MWD of 143 m and a pooled standard deviation of 111.3
m was calculated. A power of 90% and a significance level of 5% were assumed. A
drop-out of approximately 30% will be allowed, yielding a required sample size
of 51 patients (17 per group) to be randomised.

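### The trial statistician generates the allocation sequence yet is declared blinded, and the ratio is given as 1:1 for a trial with three arms

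*Protocol article*

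**What the plan says.** Everything on blinding stands in one paragraph of the protocol article, under Randomisation and blinding.

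- On who makes the list and how: "The random allocation sequence will be generated by the trial statistician on a" "1:1 basis using a computer program random number generator".
- On concealment: researchers ask the principal investigator for the allocation once baseline assessments are finished, and it comes from sealed, opaque, consecutively numbered envelopes.
- On blinding: "All outcome assessors will be blinded as will the trial statistician". The staff who deliver the exercise cannot be blinded and are kept out of analysis and reporting.

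On the number of arms, Methods and analysis says participants are "randomly allocated to 24 weeks of PF, MOD-P or MAX-P exercise with outcomes measured" at three visits. Sample size arrives at a total "of 51 patients (17 per group) to be randomised".

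**The concern.** The same role, named in the same words, both creates the allocation sequence and is said to be blinded to it. Nothing in the paragraph separates the two tasks.

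The exercise staff are unblinded, so the blinding of assessors and of the statistician is the blinding protection that the article claims. Blinding the statistician guards against analysis choices made with the arms in view, and the article leaves some room for such choices:

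- Data analysis makes one reported quantity depend on whether the distribution is judged parametric.
- It compares three time points while using the baseline value as a covariate.
- The treadmill test stops at 15 min, while maximal walking distance is defined only by stopping for pain. A patient who reaches the limit therefore needs a rule.

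A statistical analysis plan that is not shown may settle these. Until it is fixed, they are better decided by someone who does not know the arms.

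The ratio is a second, smaller matter. A two-part ratio does not describe allocation to three groups, and whoever builds the list works from that sentence.

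**Working it through.** **The planned group size.** Inputs from Sample size: difference 143 m, SD 111.3 m, power 90%, 5% significance (two-sided, from Data analysis), drop-out about 30%.

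- Standardised difference: 143/111.3 = 1.285.
- Per group for two means: 2 × (1.960 + 1.282)² / 1.285² = 12.7, rounded up to 13.
- Three groups: 3 × 13 = 39, the article's figure.
- Allowance for drop-out: 39 × 1.3 = 50.7, rounded up to 51, again the article's figure.
- Per group: 51/3 = 17, as stated.

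The planned sizes are therefore those of three equal groups, a 1:1:1 ratio. Read literally, 1:1 would split 51 into two groups of 51/2 = 25.5, which matches nothing else in the article.

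**The blinding statements side by side.** No arithmetic applies here.

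1. The statistician generates the sequence. A sequence pairs each position with an arm, and envelopes numbered in order carry those positions. The maker of the list therefore knows which arm each envelope holds.
2. The statistician is blinded. For that to be true, either the list must not show the real arms (coded labels, key held by another person), or the person who analyses must be different from the person who made the list.
3. The paragraph states neither, and it uses the same title for both tasks. Concealment by envelope does not help: it protects the person enrolling from foreseeing the next allocation, and says nothing about what the maker of the list knows.
4. Coding the dataset afterwards would not by itself restore blinding if the statistician has already seen a list with real arm names. Data collection and management says records are identified by number. If those numbers, or the baseline dates, follow the envelope order, the list can be matched to the data and the codes read off. Whether they follow that order is not stated, so this is an assumption.

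**The case against.** The strongest reply is that a statistician can generate a sequence and still be blinded. A list of arms A, B and C, with another person holding the key, achieves this, and the article does not exclude it. This stands as far as it goes. A reader might infer that blinding at analysis is impossible, and the document does not support that. What it supports is that the two statements are left unreconciled and that the arrangement as described does not provide the blinding claimed. Nor is this a detail that an article merely leaves to a fuller document, since it makes both statements itself.

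A second reply is that other protections remain: blinded assessors, exercise staff kept out of the analysis, and a named method, covariate, significance level, multiplicity adjustment and intention-to-treat principle. This also stands. It limits the consequence but does not make the blinding statement correct.

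A third is that 1:1 is loose shorthand for equal allocation. That is probably so, since the three arms and 17 per group are clear elsewhere. It makes the ratio an editorial correction, not a flaw in the design.

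A reader might also infer from the mention of a random number generator that the list is unrestricted, so that 17 per group will not be reached and power will suffer. The article does not say this. Blocked lists are made with the same tool, and block details may be left to the full protocol. With blocks of three, 51 patients give exactly 17 per arm. Even with a simple list, equal arms would be unlikely but not impossible. At the article's own effect size, a 13 v 21 split has 94.2% pairwise power against 95.3% for 17 v 17, before drop-out. No point about arm sizes or power is made here.

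**Conclusion.** The blinding statement is wrong as written. The role that makes the allocation list is declared blinded to it, and no step is described that would make this true. The ratio is also wrong as written and should be 1:1:1.

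The size of any resulting bias cannot be calculated from the documents, and no bias is shown. What is at stake is a protection that is claimed but not supported, and a statement that could not be defended in the CONSORT report which the article promises. The point is worth correcting before any outcome data are analysed. It is not a threat to the randomisation or to concealment at enrolment.

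The conclusion rests on two readings: that the trial statistician is one person in both sentences, and that this person analyses the outcomes or directs that analysis. Data analysis does not name the analyst. If someone else analyses without access to the list, the remedy is only to say so.

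**What to change.** Choose one of these arrangements and state it under Randomisation and blinding:

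- The sequence is generated by someone who takes no part in the outcome analysis.
- Or the statistician generates a list of coded arms (A/B/C), and someone else holds the key and prepares the envelopes.

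In either case, give the statistician only data with coded arms, with participant numbers that cannot be linked to the envelope sequence, until the primary analysis is complete. The unlinking matters most if the statistician has already seen a list with the real arm names. If the list already exists and this cannot be arranged, delete the claim that the statistician is blinded and report it that way.

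Change the ratio to 1:1:1.

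The cost is a small amount of a colleague's time and one or two sentences of text. Study registration says that amendments go to the research ethics committee before they are implemented, so a change to the procedure would follow that route. Sample size, outcomes and analysis model are unaffected.

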### Outcome measures

The primary outcome measure is change in maximal walking distance (MWD) at 12 and
24 weeks. Secondary outcomes include (1) pain-free walking distance (PFWD); (2)
adherence; (3) acceptability, tolerability and enjoyment of the exercise
interventions; (4) walking behaviour and physical activity; and (5) barriers to
physical activity and quality of life.

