**Analysis::**

Outcome measures will be assessed at baseline, 12 and 24 weeks adopting an
analysis of covariance (ANCOVA) to compare MWD across three time points. The
primary outcome for the trial will be change in maximal treadmill walking
distance at 12 and 24 weeks.

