### Data analysis

The primary endpoint for the statistical analysis is the change in MWD from
baseline to 12 and 24 weeks. An analysis of covariance (ANCOVA) will be used to
compare MWD across three time points with baseline MWD as a covariate. Post hoc
analysis for the main effects and interactions will be assessed using a
Bonferroni adjustment. Group differences will be compared using simple main
effects. Secondary outcomes such as PFWD distance will be evaluated adopting the
same approaches. Qualitative data will be analysed using inductive thematic
analysis whereby themes are identified from the transcripts.^
35
^

Data will be entered into SPSS (IBM, New York, USA) by a single investigator who
will maintain the overall responsibility for data quality. The primary and
secondary outcome analyses will be conducted at the conventional (two-sided) 5%
alpha level. Where parametric data distribution allows, partial eta squared
values will also be reported. To reduce the risk of false-positive claims,
secondary analyses will be considered exploratory if non-significant results are
obtained from the primary analysis. All analyses will be performed on an
intention-to-treat basis. All data will be summarised and reported in accordance
with the Consolidated Standards of Reporting Trials (CONSORT) guideline, the
template for intervention description and replication (TIDieR) and recently
published recommendations.^36–38^

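### The primary outcome covers two visits and several model effects with none named as decisive, and the rule for secondary claims depends on that unspecified result

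*Protocol article*

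**What the plan says.** Three places in the protocol article define the primary outcome, and all give two visits:

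- Abstract, Analysis: "primary outcome for the trial will be change in maximal treadmill walking" distance at 12 and 24 weeks.
- Outcome measures: "The primary outcome measure is change in maximal walking distance (MWD) at 12 and" 24 weeks.
- Data analysis: "The primary endpoint for the statistical analysis is the change in MWD from" baseline to 12 and 24 weeks.

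None ranks the visits or says whether success needs one or both.

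The Data analysis section says the ANCOVA will "compare MWD across three time points with baseline MWD as a covariate". It continues that post hoc "analysis for the main effects and interactions will be assessed using a" "Bonferroni adjustment. Group differences will be compared using simple main" effects. On the significance level, it says the primary and "secondary outcome analyses will be conducted at the conventional (two-sided) 5"% level, with no split over visits or effects. To limit false-positive claims, "secondary analyses will be considered exploratory if non-significant results are" obtained from the primary analysis.

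The Sample size section assumes 90% power and a 5% significance level, and names neither a visit nor a between-arm contrast.

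**The concern.** The trial exists to compare three pain levels. With two visits and a model that gives group, time and group-by-time effects plus simple group effects, more than one result could be reported as the primary one. Bonferroni is attached to the follow-up comparisons and not to the choice of visit or of overall effect. A between-arm difference at 12 weeks only, at 24 weeks only, on average over visits, or as an interaction could each be presented as a positive trial at the full 5%.

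The same gap passes to the secondary outcomes. The rule that labels them exploratory turns on whether the primary analysis is significant, but that analysis is not reduced to one test. Every arm exercises, so a significant change over time is expected whether or not the pain levels differ. If such a result were taken as a significant primary analysis, the rule would give no protection.

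**Working it through.** **1. The plan's own sample size.** Inputs from Sample size: change 143 m, SD 111.3 m, power 90%, alpha 5%. For two means, n per arm = 2 × (1.960 + 1.282)² × (111.3/143)² = 2 × 10.51 × 0.606 = 12.7, so 13. Three arms give 39, and 39 × 1.3 = 50.7, so 51. The stated figures therefore reproduce as one test at 5%, with no allowance for a second visit.

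**2. False-positive rate with no arm difference.** For two independent tests at 5%: 1 − 0.95² = 9.75%. The two visits share patients and are correlated, so this was simulated with a baseline-adjusted ANCOVA and three arms of 13 or 17. The correlation between week-12 and week-24 residuals is not given in the article. It is assumed to lie between 0.5 and 0.95.

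| What counts as a positive primary result | Rate with no arm difference |
|---|---|
| Between-arm test at one named visit | 5% |
| Between-arm effect at either visit, each at 5% | about 7 to 9.5% |
| Either visit, or group main effect, or group-by-time interaction | about 11 to 14% |
| Between-arm effect required at both visits | about 1 to 4% |
| Either visit, each at 2.5% | at or below 5% |

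The either-visit rate falls as the correlation rises. At 0.95, separate runs gave between 6.1% and 6.9%, so the lower end is approximate. A further simulation assumed equal correlations r of 0.5 to 0.9 among all three measurements. Given baseline, this leaves a residual correlation of r/(1 + r), that is 0.33 to 0.47. It gave 9.1 to 9.4% for either visit and 0.4 to 0.8% for both.

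**3. The time effect.** Suppose baseline is one level of the time factor, and take 143 m and 111.3 m as the mean and SD of change (an assumption). The overall change then lies (143/111.3) × √n standard errors from zero. Thirty per cent loss from 51 leaves 51 × 0.7 = 35.7, or 36 patients: 1.285 × √36 = 7.7. With 39 evaluable: 1.285 × √39 = 8.0. Power is above 0.999 in both cases. If baseline is only the covariate, the time effect compares week 12 with week 24, and 143 m says nothing about its size.

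**4. Sample size under the possible repairs.** One named test at 5% keeps 39 and 51. If either visit may win at 2.5% each, n per arm = 2 × (2.241 + 1.282)² × 0.606 = 15.04, so 16, or 48 evaluable (48 × 1.3 = 62.4, so 63 by the article's own inflation). An F test with one arm differing needs 45 evaluable. Staying at 39 evaluable with 2.5% each gives power of about 0.85.

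**The case against.** The strongest reply is that the article condenses a fuller protocol, that a statistical analysis plan may exist, and that an analyst would take the between-arm comparison as primary, since the objective is to compare pain levels directly. The last part is fair as a guess at intent. But the article itself fixes the two-visit endpoint, the multi-effect model, the unsplit 5% and the rule for secondary outcomes, and together these do not identify one test.

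Several stronger readings are tempting and are not supported:

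- **That the false-positive rate is above 5%.** It depends on an unstated success rule. If both visits are required, the rate is below 5%. The simple group effects are mentioned directly after the Bonferroni sentence, so they may be meant as adjusted follow-up.
- **That the rule for secondary outcomes will be satisfied whatever happens.** This needs a time effect to count as success and baseline to be a time level. The wording does not exclude that, but does not state it, and the stated aim points the other way.
- **That a large error rate can be computed across the secondary outcomes.** Acceptability, tolerability and enjoyment are assessed by interview and have no test. The number of tests on the other outcomes is not given, the scores come from the same patients, and any such figure applies only once the primary result is significant. That all secondary outcomes then become confirmatory is an inference from a rule that states only the opposite case.
- **That 12 weeks is the lesser visit.** The opening of Methods and analysis gives generalisability as the reason for measuring at 12 and 24 weeks and does not rank them. The Introduction notes that guidelines generally advocate a 3-month programme.

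**Conclusion.** The concern holds in a limited form. The article leaves the decisive primary test undefined, so its stated 5% is not secured. The size depends on the success rule: about 7 to 9.5% if either visit may count, about 11 to 14% if the group main effect or interaction may also count, and below 5% if both visits must succeed. These figures rest on the assumed residual correlation of 0.5 to 0.95 and on reading group, time and group-by-time into the article's general reference to main effects and interactions.

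The rule for secondary outcomes inherits the gap. A time effect is not excluded by its wording and, under the assumptions shown, would be about 8 standard errors from zero with 36 to 39 patients without bearing on pain level. A reader might conclude that the trial will certainly over-claim. The article supports only the weaker statement that it does not prevent this. The point should be corrected before analysis.

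**What to change.** Name one deciding test: the baseline-adjusted between-arm effect on MWD at one visit, at two-sided 5%. Twenty-four weeks, the end of the randomised programme, is the natural choice, though the ranking is the sponsor's to make. Do the Bonferroni pairwise comparisons only if that test is significant, and test the other visit next in fixed sequence. State that the rule for secondary outcomes refers to this between-arm test and not to any time effect.

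This changes wording only and leaves 39 evaluable and 51 randomised. The price is that an effect seen only at the second-ranked visit supports no confirmatory claim. If both visits are to stay co-primary, split alpha at 2.5% each and accept power of about 0.85 at 39 evaluable, or raise the evaluable number to 45 to 48. Alternatively, state that both visits must succeed, which controls the error rate but makes success harder to reach.

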### Outcome assessments

Clinical examination will include a review of past medical history and current
medications, height, weight and cardiovascular risk factor assessment, that is,
resting blood pressure and smoking status. Walking behaviour and physical
activity will be recorded over a 7-day period, at baseline (1 week prior to
commencing the SEP) and at 12 weeks and 24 weeks using an ActiGraph GT9X link
activity monitor (ActiGraph, Pensacola, FL, USA). A valid wear time is defined
as 4>days of >10 h of wear. Periods of >60 min of consecutive zero
reading will be considered as non-wear time. Activity intensities will be
assigned adopting cut points on those validated in coronary artery disease populations,^
25
^ with light, moderate and vigorous classified as <1800 counts/min,
1800–3799 counts/min and >3800 counts/min, respectively. Sedentary bouts will
be defined as periods of wear time exceeding 60 min at <150 counts/min.

A graded treadmill walking test will be performed to determine MWD and PFWD. The
treadmill protocol will consist of a constant speed of 3.2 km/h and incremental
gradient beginning at 0% increasing 2% every 2 min, for a maximum of 15 min^
26
^ and will be conducted in accordance with published recommendations for
implementation, ensuring standardisation.^
27
^ PFWD will be recorded at the point at which the patient first indicates
the onset of claudication pain. MWD will be recorded when the patient can no
longer continue due to claudication pain.

Adherence and compliance will be determined by recording the number of training
sessions attended and successfully completed in accordance with the exercise
protocol. Drop-out from the SEP will also be documented for all study groups in
addition to the reason for drop-out, where provided voluntarily by
participants.

Quality-of-life measures will be recorded using disease-specific questionnaires.
The King’s College Vascular Quality of Life, a 25-item questionnaire with five
domains (pain, symptoms, activities, social and emotional), and the Walking
Impairment Questionnaire (WIQ) will be used to assess the perceived impact of
claudication.^28,29^ Personal and environmental barriers to physical
activity in PAD will be based on the studies by Barbosa *et al.*^
12
^ and Cornelis *et al.*^
30
^ A 5-point ordinal scale (never, seldom, sometimes, frequently, always)
will be used to assess the limiting character of each barrier (see Table 1).^
30
^ To verify the safety of the interventions performed in the SEP, adverse
and serious adverse events will be carefully monitored, recorded and reported in
line with the principles of Good Clinical Practice (GCP). Semi-structured
interviews adopting a predetermined set of open topics will qualitatively
evaluate acceptability, tolerability and enjoyment of the exercise intervention
in all groups

**Table 1. table1-17539447221108817:** Personal and environmental barriers.

Personal	Environmental
Pain on exertion	Obstacles aggravating pain
Need for rest	Unfavourable weather
Fear of falling	Poor quality or dangerous side walks
Lack of knowledge regarding exercise benefits	No place to rest when experiencing pain
Need for supervision/control	Shortness of space to exercise or be physically active
Lack of time	Hilly terrain
Other health issues	
Financial reasons	

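### Light activity is defined without a lower bound and overlaps the 150 counts/min sedentary threshold, so light-activity time is inflated as written

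*Protocol article*

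**What the plan says.** All the rules stand in the Protocol article, Outcome assessments, in the paragraph on the activity monitor.

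- **Intensity.** The classes are "with light, moderate and vigorous classified as <1800 counts/min" for light, then "1800–3799 counts/min and >3800 counts/min, respectively". They are said to be "assigned adopting cut points on those validated in coronary artery disease populations".
- **Sedentary bouts.** These are to "be defined as periods of wear time exceeding 60 min at <150 counts/min".
- **Non-wear.** "Periods of >60 min of consecutive zero" are treated as follows: the "reading will be considered as non-wear time". Zero runs of 60 min or less therefore stay in wear time.

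No sentence removes minutes below 150 counts/min from light, and none sets a sedentary class minute by minute. Under Outcome measures, walking and physical activity is secondary outcome (4). The primary outcome is separate: "The primary outcome measure is change in maximal walking distance (MWD) at 12 and" 24 weeks.

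**The concern.** Intensity classes should put each worn minute in exactly one class. Here light reaches down to zero, while the sedentary definition uses a threshold inside the same range and applies only to long runs. An analyst following the text has to count short-spell sitting as light activity, and has to decide unaided whether a minute in a long sedentary bout is counted once or twice.

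What is at stake is the meaning of light-activity time in a trial of walking exercise. A plausible benefit is that patients sit less and move about gently more. If both states fall in one class, light-activity time cannot show that change.

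**Working it through.** **Inputs.** From Outcome assessments: light <1800, moderate 1800 to 3799, vigorous >3800 counts/min; sedentary bout <150 counts/min for more than 60 min of wear; non-wear is more than 60 min of consecutive zeros. The plan gives no minutes per class, so there is no figure of its own to reproduce.

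**Step 1: apply the rules literally.**

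| Counts/min | Run of 20 or 60 min | Run of 61 min |
|---|---|---|
| 0 | light | non-wear |
| 50 or 149 | light | light and sedentary bout |
| 150 or 1799 | light | light |
| 1800 or 3799 | moderate | moderate |
| 3800 | no class | no class |
| 3801 | vigorous | vigorous |

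The overlap is in the second row (longer runs). The sitting time that is left to light alone is in the first two rows (shorter runs).

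**Step 2: what light time then measures.** Let W be wear time, M moderate plus vigorous time and S all worn time below 150 counts/min, in min/day. Ignoring minutes at exactly 3800:

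- as written, light = W − M
- with a floor at 150, light = W − M − S

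As written, light time is simply the wear time that is not moderate or vigorous. S does not enter it.

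**Step 3: sensitivity to change.** Suppose 30 min/day moves from sitting in short spells (0 to 149) to light movement (150 to 1799), with W and M unchanged.

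- as written: change in light = −30 + 30 = 0
- with the floor: change in light = +30, and change in S = −30

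**Step 4: possible size, on assumed inputs.** Assume M = 20 min/day, W = 600 or 840 min/day, and S equal to 40% or 70% of W. None of these figures comes from the documents.

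| W | S | Light as written (W − 20) | Light with floor (W − 20 − S) |
|---|---|---|---|
| 600 | 0.4 × 600 = 240 | 580 | 340 |
| 600 | 0.7 × 600 = 420 | 580 | 160 |
| 840 | 0.4 × 840 = 336 | 820 | 484 |
| 840 | 0.7 × 840 = 588 | 820 | 232 |

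Removing only the long sedentary bouts from light would not cure this. If half of S lay in such bouts, light would be 580 − 120 = 460 or 580 − 210 = 370 for W = 600, and 820 − 168 = 652 or 820 − 294 = 526 for W = 840. Each is still above the value with the floor. M is the same in every row.

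**The case against.** The strongest reply is that this is a condensed article. The cut points come from a cited validation source that may set a floor for light activity, and the software may apply it. The sentence on bouts can also be read as an added summary, with 150 understood as the general sedentary cut point. Part of this stands: wrong processing of the data is not shown, and the source cannot be checked here. It does not remove the point, because the article does not leave the bounds to another document. It prints numerical limits for all three classes and a 150 threshold beside them, and as printed they overlap.

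Several stronger readings are tempting, but the documents do not support them.

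- *The physical-activity outcome as a whole is misclassified.* It is not. Moderate and vigorous time and sedentary bouts keep their definitions, and the bout measure can still register a change in sitting that occurs in long runs.
- *Total sedentary time will be understated by a stated number of hours.* The text defines bouts. It does not say that total sedentary time is limited to them, and any hours are assumed.
- *The outcome cannot show benefit.* Outcome measures does not name light minutes as the summary to be analysed, so the loss applies to light time and to totals that include it.
- *One arm is favoured.* The same rules apply to all three groups. The demonstrated loss is of sensitivity.

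The gap at exactly 3800 and the garbled minimum number of wear days are clerical. Counting long zero runs as non-wear is a processing choice. None of these adds weight to the point.

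**Conclusion.** Wrong as written, and minor. The light class has no floor, overlaps the sedentary-bout definition, and takes in all worn time below 150 counts/min in runs of 60 min or less. Light-activity time, and any total built on it, is inflated and does not respond to a move from short-spell sitting to light movement.

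The size cannot be computed from the documents. The figures in Step 4 show only what the rule would do under assumed activity patterns. The conclusion assumes that the printed limits are applied literally; a floor in the cited source, if used in processing, would remove the effect in the data but not the fault in the text. One part of one secondary outcome is affected. The primary outcome, treadmill walking distance, does not depend on these rules.

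**What to change.** First check the 150 counts/min floor against the cited cut-point source. Then state classes that are exclusive and complete, using the protocol's own thresholds:

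- sedentary: <150 counts/min
- light: 150 to 1799 counts/min
- moderate: 1800 to 3799 counts/min
- vigorous: ≥3800 counts/min

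Report sedentary time minute by minute over valid wear, and keep bouts longer than 60 min as a further measure. Say that minutes in those bouts are part of sedentary time and are not counted as light. The cost is a change of wording and of accelerometer software settings. No new data are needed.
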